#### 6.3 TREATMENT COMPLIANCE

The trial center staff will maintain a record of all investigational medicinal products administered. An inventory is taken of the study drug supplies for each subject and a balance is maintained by using a drug accountability log. The study drug is administered as a subcutaneous injection only by qualified study center personnel and the details of each injection are documented in the source documents and case report form (CRF) including date, start and stop times of subcutaneous injection and injected volume. Further details are described in chapter 11.

#### 6.4 PRESTUDY AND CONCOMITANT MEDICATION

The permitted and prohibited pre-therapies and the washout times, if applicable, are defined in the inclusion and exclusion criteria.

#### 6.4.1 GLUCOCORTICOID THERAPY

The use of glucocorticoids for the indication SLE is allowed to a maximum of 20mg daily prednisolone (or equivalent) throughout the study. The glucocorticoid dosage must be stable from baseline until Week 12 (primary endpoint study visit). After Week 12 (primary endpoint visit), it is possible to reduce the glucocorticoid dosage if the disease activity allows tapering, according to the judgment of the treating physician.

#### 6.4.2 DISEASE-MODIFYING DRUGS

Background disease-modifying drugs must be continued throughout the study at stable doses even if participants achieve a state of low-disease activity (LLDAS) or remission, except for glucocorticoids, that are allowed to be tapered (see 6.4.1 GLUCOCORTICOID THERAPY). For the treatment of flares or ongoing disease activity, rescue medication is allowed according to section 6.5 RESCUE MEDICATION.

#### 6.4.3 IMMUNGLOBULIN SUBSTITUTION

The use of intravenous immunoglobulins (IVIG) is allowed throughout the study as substitution in case of hypogammaglobulinemia, according to current guidelines and recommendations. Secondary immunodeficiencies (SID), in particular hypogammaglobulinemia, may result from treatment with novel targeted drugs for malignant and non-malignant diseases (e.g. CD19, CD20, CD52 antibodies, BCL2, kinase and mTOR inhibitors, chemotherapy, and immunotherapeutics) [59]. The resulting infectious complications are associated with an increased risk of morbidity and mortality in immunodeficient patients. Therefore, the European Conference on Infections in Leukemia (ECIL) recently published a position paper on infections associated with various immunotherapeutic and molecular agents [60]. Appropriate diagnosis and treatment of SID, taking into account individual risk factors, is essential to ensure quality of care. Comprehensive monitoring of the diagnosis and treatment of SID in such patients in everyday clinical practice is therefore essential. The recently published DGHO (German Society for Hematology and Medical Oncology) oncopedia guideline on therapy-induced SID (<https://onkopedia.com/de/onkopedia/guidelines/immunundefekte-sekundaer/@@guideline/html/index.html>) as well as guidelines on chronic lymphatic leukemia [61], multiple myeloma [62], the cross-sectional guideline of the German Medical Association (Bundesärztekammer) [63] and European experts [64] recommend immunoglobulin G (IgG) substitution in patients with antibody deficiency and clinically relevant susceptibility to infection.

#### 6.4.4 TOPICAL MEDICATIONS

Study participants must not use topical preparations of glucocorticoids.

### 6.5 RESCUE MEDICATION

For the treatment of disease flares, defined according to the SLEDAI-flare index (SFI), administration of glucocorticoids is allowed up to a maximum dose of 100mg/day. In case of recurring flares or ongoing disease activity, defined as a state of not achieving low disease-activity (LLDAS), administration of additional disease-modifying drugs is allowed from Week 12 (primary endpoint visit) (except for medications listed in section 6.6 PROHIBITED THERAPIES).

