- Change from baseline in serum complement factors for C3 and C4 by visit. Time frame: baseline, and follow-up visits of the core study period at Week 3, 5, 7, 9, 12, 16, 20, 24, 28, 32, 36, and at Week 42, 48, 54, 60, 66, 72, 78 and 84 of the LTE observational period.
- Change from Baseline in levels of protective vaccine-induced serum antibody titers for Tetanus toxoid, Diphtheria and Measles by visit. Time frame: baseline, and follow-up visits of the core study period at Week 3, 5, 7, 9, 12, 16, 20, 24, 28, 32, 36, and at Week 42, 48, 54, 60, 66, 72, 78 and 84 of the LTE observational period.

3. To evaluate whether daratumumab treatment is associated with clinical efficacy and glucocorticoid sparing, the following secondary outcome measures will be analyzed:

- Proportion of subjects with a SLE responder index of 4 (SRI-4), SRI-4 being defined as (1) a  $\geq 4$ -point reduction in SELENA-SLEDAI score as compared to baseline, and (2) no new BILAG A score or  $\leq 1$  new BILAG B score, and (3) no deterioration from baseline in the physician's global assessment by  $\geq 0.3$  points, at Week 12 (4 weeks after the last daratumumab injection). Time frame: Week 12.
- Proportion of subjects with a SLE responder index of 4 (SRI-4), SRI-4 being defined as (1) a  $\geq 4$ -point reduction in SELENA-SLEDAI score as compared to baseline, and (2) no new BILAG A score or  $\leq 1$  new BILAG B score, and (3) no deterioration from baseline in the physician's global assessment by  $\geq 0.3$  points, by visit. Time frame: baseline, and follow-up visits of the core study period at Week 3, 5, 7, 9, 12, 16, 20, 24, 28, 32, 36, and at Week 42, 48, 54, 60, 66, 72, 78 and 84 of the LTE observational period.

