## 6.6 PROHIBITED THERAPIES

Use of additional immunosuppressants or immunomodulators, other than those explicitly allowed in the inclusion/exclusion criteria are prohibited including, but not limited to, the following:

- Agents targeted at reducing TNF (e.g. infliximab, golimumab, certolizumab pegol, etanercept, and adalimumab)
- B-cell depleting agents (e.g. rituximab, obinutuzumab or ocrelizumab)
- Interleukin-1 inhibitors (e.g. canakinumab)
- IL-1 receptor antagonist (e.g. anakinra)
- Interleukin-2 inhibitors or exogenous IL-2 therapy
- Tocilizumab or any other biologic targeting IL-6 or IL-6 receptor
- Tofacitinib, baricitinib, filgotinib, upadacitinib or any other janus kinase (JAK) inhibitors
- Abatacept
- Anti-IL-17 agents (e.g. secukinumab or ixekizumab)
- Anti-IL-23 agents (e.g. guselkumab)
- Leflunomide
- Tacrolimus or other immunomodulatory oral or topical preparations
- Thalidomide or lenalidomide
- Dapsone

Use of cytotoxic drugs is prohibited including, but not limited to, cyclophosphamide, chlorambucil, nitrogen mustard, or other alkylating agents. Multiple administrations of high doses of oral glucocorticoids (average daily dose  $\geq 20$  mg), or initiation of high potency topical glucocorticoids, are prohibited during the study. Sulfa-based antibiotics, where reasonable, should generally be avoided. The use of complementary therapies (e.g. herbs, ointments, traditional Chinese medicine, and acupuncture) that have the potential to activate or inhibit the immune system is prohibited. In addition, use of complementary therapies that have the potential to interact with antithrombotic agents is prohibited in those taking antithrombotic agents. The use of other complementary therapies is strongly discouraged; in individual cases, use may be permitted following discussion with the study sponsor and/or medical monitor.

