### 7.2.3 SELENA-SLEDAI FLARE INDEX

One key secondary objective is to assess the flare rate in daratumumab treated patients. The corresponding secondary endpoint of this study is the time to first severe flare as measured by the modified SELENA-SLEDAI SLE Flare Index (SFI) [68]. This index categorizes SLE flares as either “mild or moderate” or “severe” based on six variables:

- change in SLEDAI-2K score from most recent assessment to current,
- change in signs or symptoms of disease activity,
- change in prednisone (or equivalent) dose,
- use of new medication for disease activity or hospitalization,
- change in PGA score,
- hospitalization for SLE activity (severe flare only).

The modified SELENA-SLEDAI SFI requires that a patient who has a SLEDAI score  $>12$  is considered as having a severe flare only if they have one other component present. This modification was made

because participants entering the trial with high disease activity (i.e.  $\geq 11$ ) could too easily trigger a severe flare by minor increases in SLEDAI score.

Lupus flares should be treated primarily with medications listed in the section 6.5 RESCUE MEDICATION. Only in case of insufficient response to such therapies and presence of severe SLE organ manifestations, medications listed in section 6.6 PROHIBITED MEDICATION can be used. In this situation, the participant will be considered as treatment failure but will not need to be withdrawn from the study (see section 8.2 DISCONTINUATION OF STUDY TREATMENT). To ensure that the interpretability of SLE FLARE INDEX will not be impacted by prohibited medication, such patients will be included in the intention-to-treat analysis set (see section 9.3. ANALYSIS SETS), similar to patients with a dose interruption in case of adverse events.

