### 7.3.4 SLE FLARE INDEX

For this study, SLE flares will be defined as follows:

SLEDAI-2K flare is defined as at least 1 new SLEDAI-2K mild/moderate or severe flare compared with baseline as assessed using the SLEDAI flare index (SFI).

Severe SLEDAI-2K flare is defined as presence of one or more of the following:

- Increase in SLEDAI-2K score to greater than 12. If this is the only criteria met, at least one additional criterion below must also be present to be considered a severe SLEDAI-2K flare
- New/Worse SLE activity (CNS, vasculitis, nephritis, myositis, thrombocytopenia ( $< 60,000/\text{mm}^3$ ), hemolytic anemia (hemoglobin  $< 7$  g/dL or decrease in hemoglobin  $> 3$  g/dL) requiring one or more of the following: (1) increase in prednisone (or equivalent) dose to  $> 0.5$  mg/kg/day, (2) a doubling or greater of prednisone (or equivalent) dose, (3) addition of a new systemic immunosuppressant agent (cyclophosphamide, AZA, MTX, MMF, belimumab, rituximab, or other systemic immunosuppressant therapy), or (4) hospitalization for SLE activity
- Increase in prednisone (or equivalent) to  $> 0.5$  mg/kg/day for SLE activity
- New cyclophosphamide, AZA, MTX, MMF, belimumab, rituximab (or other systemic immunosuppressant therapy) for SLE activity
- Hospitalization for SLE activity
- Increase in the 0-3 VAS anchored PGA score to  $> 2.5$

Mild/moderate SLEDAI-2K flare is defined as presence of one or more of the following:

- Increase in SLEDAI-2K score of 3 points or more (but not to more than 12)
- New/worse SLE activity (discoid, photosensitive, profundus, cutaneous vasculitis, bullous lupus, nasopharyngeal ulcers, pleuritis, pericarditis, arthritis, fever due to SLE)
- Increase in prednisone (or equivalent), but not to  $> 0.5$  mg/kg/day, for SLE activity
- Added NSAID or hydroxychloroquine (or other antimalarial therapy) for SLE activity
- Increase in the 0-3 VAS anchored PGA score by  $\geq 1$ , but not to more than 2.5

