### 7.3.7 GLUCOCORTICOID DOSAGE

In this study, tapering of the glucocorticoid dosage administered for the indication SLE is allowed after Week 12 (primary end point visit), if justified according to the judgment of the treating physician (See section 6.4.1 GLUCOCORTICOID THERAPY). This allows investigating the steroid sparing effect of the study drug, and steroid reduction is one of the secondary endpoints, as advocated by leading experts in managing lupus [83]. The glucocorticoid dosage must be stable until Week 12 and may be tapered thereafter. The average reduction of oral glucocorticoid will be analyzed at baseline, and follow-up visits of the core study period at Week 3, 5, 7, 9, 12, 16, 20, 24, 28, 32 and 36, and Week 42, 48, 54, 60, 66, 72, 78 and 84 of the LTE observational period.

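### Flare rescue with up to 100 mg/day glucocorticoid before Week 12 conflicts with the 20 mg/day cap and stable-dose rule, and a rescued patient can still count as a Week 12 SRI-4 responder

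*Protocol*

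**What the plan says.** **Dose rules.** Section 6.4.1: "The use of glucocorticoids for the indication SLE is allowed to a maximum of 20mg daily prednisolone (or equivalent) throughout the study". It adds: "The glucocorticoid dosage must be stable from baseline until Week 12 (primary endpoint study visit"). Section 7.3.7 repeats the second rule: "The glucocorticoid dosage must be stable until Week 12 and may be tapered thereafter". Section 6.6 lists among the prohibited therapies "Multiple administrations of high doses of oral glucocorticoids (average daily dose" of 20 mg or more), without saying over what period the average is taken.

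**Rescue.** Section 6.5 covers flares defined by the SLEDAI flare index (SFI), for which "administration of glucocorticoids is allowed up to a maximum dose of 100mg/day". The Week 12 start in 6.5 stands in the following sentence and applies only to additional disease-modifying drugs. Section 6.4.2, on background disease-modifying drugs, refers flares and ongoing activity to 6.5. Section 7.2.3 makes this the first line: "Lupus flares should be treated primarily with medications listed in the section 6.5 RESCUE MEDICATION".

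**Failure labels.** Section 7.2.3 calls a patient a treatment failure when a 6.6 drug is used after insufficient response to 6.5 treatment. Section 8.2 does so when a new permitted immunomodulator is started; a glucocorticoid increase is not named.

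**Endpoint.** Section 3.2.3 lists "Proportion of subjects with a SLE responder index of 4 (SRI-4), SRI-4 being defined as" a SLEDAI reduction of at least 4 points, a BILAG condition and a physician's global assessment (PGA) condition. Section 7.3.3 gives the same three components. Section 9.5.2 reports the number achieving SRI-4 at Week 12, and 9.3 puts all enrolled patients in the main analysis.

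**The concern.** There are two linked problems. First, an investigator who sees a flare before Week 12 has two written ceilings, 20 and 100 mg/day, and a stable-dose rule that any rescue would break. A statistical analysis plan cannot settle this, because it is a dosing instruction.

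Second, the study has no control group, and Week 12 SRI-4 is the first clinical result named in 9.5.2, where it is presented as following from daratumumab. A steroid increase given for a flare can itself improve SLEDAI, BILAG and PGA. If it does, the patient is counted as a responder to the study drug although the need for rescue is evidence against response. With ten patients, one such case is visible in the rate.

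**Working it through.** No figure in the protocol is disputed, so there is none to reproduce. The check compares the text, then works out the look-back, the 6.6 threshold and the weight of one patient.

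**1. Do the dose rules conflict?**

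| Section | Limit | Period | Flare exception stated |
|---|---|---|---|
| 6.4.1 | 20 mg/day | whole study | no |
| 6.4.1, 7.3.7 | stable dose | to Week 12 | no |
| 6.6 | no repeated oral doses averaging 20 mg/day or more | whole study | no |
| 6.5 | 100 mg/day for SFI flares | no start week | it is the rescue rule |

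That 6.5 applies before Week 12 is inferred from the missing start week for glucocorticoids beside an explicit one for other drugs. The stable-dose rule is further weakened by 7.3.4, where "Increase in prednisone (or equivalent), but not to" above 0.5 mg/kg/day, when made for SLE activity, is by itself a mild/moderate flare; an SFI flare is what opens 6.5.

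**2. Does rescue always breach 6.6?** No. For d days at 100 mg in a window of w days, with background b mg/day:

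average = (100d + b(w − d)) / w

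Both b (0 to 5 mg/day) and w are assumptions, since the protocol gives neither. The smallest d that reaches 20 mg/day is:
- w = 7: d = 2
- w = 14: d = 3
- w = 28: d = 6 for b = 0, and d = 5 for b = 5

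Three days in a 28-day window with b = 5 gives (300 + 125)/28 = 15.2 mg/day, which is below the limit. So the same course may or may not be prohibited, depending on an unstated window.

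**3. Does the look-back catch an early rescue?** In the visit schedule Week 12 is Day 77 and Week 5 is Day 28.
- SLEDAI-2K, 30 days (7.2.2): 77 − 30 = Day 47
- SLEDAI-2K, 10 days (form in the attachments): 77 − 10 = Day 67
- BILAG, 4 weeks (7.2.4): 77 − 28 = Day 49

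A flare treated at Day 28 and resolved before Day 47 is scored by neither index at Week 12. The 10-day form shortens the SLEDAI reach further.

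**4. Does any rule turn rescue into SRI-4 non-response?** SRI-4 has no medication component in 3.2.3 or 7.3.3. The failure labels in 7.2.3 and 8.2 are not linked to SRI-4 anywhere. Section 9.3 keeps the patient in the main analysis. The answer is no.

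**5. Weight of one patient.** At N = 10, 1/10 = 10 percentage points. In the complete-case sensitivity analysis, if the protocol's assumed 50% drop-out leaves 5 patients, 1/5 = 20 points.

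An assumed example with exact (Clopper-Pearson) 95% intervals:
- 6/10: 26% to 88%
- one of the six rescued, 5/10: 19% to 81%
- two of the six rescued, 4/10: 12% to 74%

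**6. How likely is at least one?** The protocol gives no rescue rate. Assume that a share r = 10% to 30% of patients is rescued before Week 12 and that a share c = 30% to 100% of those meets SRI-4. The expected number is 10rc, from 0.3 to 3.0. The chance of at least one is 1 − (1 − rc)^10: 1 − 0.97^10 = 26% at the low end and 1 − 0.70^10 = 97% at the high end. The range shows only that the assumption decides the answer.

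**The case against.** **Rescue is an implied exception.** Section 6.4.2 sits between 6.4.1 and 6.5 and refers flares to 6.5, so the protocol can be read as a general rule with a specific exception. This is plausible, and it makes the conflict one of wording. But the pointer stands in the section on disease-modifying drugs and leaves the 6.4.1 cap, the 7.3.7 rule and the 6.6 prohibition as they are. It also makes early steroid rescue permitted, which leaves the SRI-4 problem in place. If 6.4.1 governs instead, the increase is a protocol deviation to be tabulated under 9.1.5, and the SRI-4 count is again unchanged.

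**The rescue is not hidden.** A reader might infer that the plan overlooks rescued patients. It does not: under 7.3.4 a prednisone increase for SLE activity is a flare, so it enters the time-to-flare analysis in 9.5.2. LLDAS has a 7.5 mg/day limit, doses are summarised by visit, and 9.1.6 lists medication increases. With ten patients the rescued ones can be identified. This lowers the stakes but does not correct the responder count.

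**A rescued patient might be a failure.** A reader might also infer that a steroid-rescued patient can never be called a treatment failure. That is too strong. A course averaging 20 mg/day or more may fall under 6.6 and so under the 7.2.3 label, and the modified intention-to-treat analysis excludes patients who stop study treatment for use of prohibited medication. Neither step makes the patient an SRI-4 non-responder in the main analysis.

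**This belongs in the SAP.** Rules for intercurrent events often do. Here, however, the protocol itself fixes the responder definition, the failure labels and the Week 12 count, and together they give an answer.

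**Attribution stays confounded anyway.** Under 6.2.2 all patients receive dexamethasone 20 mg before the first two doses and 10 mg before later ones if no injection reaction occurred; some also receive post-dose methylprednisolone under 6.2.3. That stands, and no rescue rule removes it. The difference is that those steroids are scheduled, whereas rescue is triggered by a flare.

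**Conclusion.** The point holds in a limited form. The dose rules conflict as written, even if an exception was intended. Independently of which rule governs, a patient rescued with steroids before Week 12 who meets the three SRI-4 components is counted as a Week 12 responder in the main analysis.

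The size is 10 percentage points per such patient at N = 10. The number of such patients is unknown, so the documents do not support saying that the SRI-4 rate will be inflated, only that it can be. A rescued patient must still meet all three components. SRI-4 is a descriptive secondary endpoint, no confirmatory test is planned, and the intervals in the example overlap widely. The conclusion rests on reading the missing start week in 6.5 as permission before Week 12. The change is worth making because it is cheap and the study has no control arm against which to judge the rate.

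**What to change.** 1. State flare rescue under 6.5 as an explicit exception in 6.4.1, 6.6 and 7.3.7, and give 6.6 an averaging window. Alternatively, restrict glucocorticoid rescue before Week 12; that choice is clinical.
2. In 7.3.3 and 9.5.2, score as a Week 12 SRI-4 non-responder any patient who before Week 12 received glucocorticoid rescue under 6.5, a new immunomodulator or a 6.6 drug. Exclude the pre- and post-dose steroids of 6.2.2 and 6.2.3 from this rule.
3. Report the unmodified three-component SRI-4 as a sensitivity result.

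The cost is a few sentences in five sections and one extra table row. No new data are needed, since concomitant therapy is already recorded at the study visits. The downside is that a true responder with a brief or small rescue is counted conservatively; the sensitivity row shows by how much. The scheduled dexamethasone still confounds attribution to daratumumab, and the report should say so.

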## 6.6 PROHIBITED THERAPIES

Use of additional immunosuppressants or immunomodulators, other than those explicitly allowed in the inclusion/exclusion criteria are prohibited including, but not limited to, the following:

- Agents targeted at reducing TNF (e.g. infliximab, golimumab, certolizumab pegol, etanercept, and adalimumab)
- B-cell depleting agents (e.g. rituximab, obinutuzumab or ocrelizumab)
- Interleukin-1 inhibitors (e.g. canakinumab)
- IL-1 receptor antagonist (e.g. anakinra)
- Interleukin-2 inhibitors or exogenous IL-2 therapy
- Tocilizumab or any other biologic targeting IL-6 or IL-6 receptor
- Tofacitinib, baricitinib, filgotinib, upadacitinib or any other janus kinase (JAK) inhibitors
- Abatacept
- Anti-IL-17 agents (e.g. secukinumab or ixekizumab)
- Anti-IL-23 agents (e.g. guselkumab)
- Leflunomide
- Tacrolimus or other immunomodulatory oral or topical preparations
- Thalidomide or lenalidomide
- Dapsone

Use of cytotoxic drugs is prohibited including, but not limited to, cyclophosphamide, chlorambucil, nitrogen mustard, or other alkylating agents. Multiple administrations of high doses of oral glucocorticoids (average daily dose  $\geq 20$  mg), or initiation of high potency topical glucocorticoids, are prohibited during the study. Sulfa-based antibiotics, where reasonable, should generally be avoided. The use of complementary therapies (e.g. herbs, ointments, traditional Chinese medicine, and acupuncture) that have the potential to activate or inhibit the immune system is prohibited. In addition, use of complementary therapies that have the potential to interact with antithrombotic agents is prohibited in those taking antithrombotic agents. The use of other complementary therapies is strongly discouraged; in individual cases, use may be permitted following discussion with the study sponsor and/or medical monitor.

## 7 STUDY EVALUATIONS

### 7.1 STUDY PROCEDURES

The current SARS-CoV-2 pandemic leads to changes from the routine procedures of study visits and to the following regulations: Patients must undergo a SARS-CoV-2 rapid test prior to each study visit (either to bring a test no older than 24 hours or a rapid test will be performed on site). Depending on the SARS-CoV-2 incidence rate and the current operating guidelines, it must be weighed whether the currently prevailing risk of infection for the patient is increased by an on-site visit. This is the case for all patients not fully vaccinated against SARS-CoV-2. For these patients, visits not including study drug administration (weeks 16 through 32) may be replaced by remote (video) visits. SARS-CoV-2 infection of study participants will automatically lead to study drug discontinuation but not necessarily to study termination. Rather, the follow-up phase can be continued once quarantine/COVID-symptoms/SARS-CoV-2 PCR positivity have resolved.

The study-specific procedures for each patient visit at the study site are shown in the following table.

